### Data Collection and Management

Data entry, including quality checks and double entry validation, will be performed through eCRF (Multimedia Appendix 1). Missing data from the unit record will be compared with the corresponding handwriting case record form and corrected accordingly.

### Statistical Analysis

Descriptive statistics will be used to evaluate differences between the 2 groups of participants. The study hypotheses will be tested using an intention-to-treat analysis, where all consenting patients who were randomized during the accrual period will be included in the analysis.

Continuous data will be summarized using count, mean, median, SD, and IQRs, whereas categorical measures will be described using frequencies. The assumption of normality will be tested with the Shapiro-Wilk test. Pre-post effects within groups will be investigated using the paired *t* test or the Wilcoxon matched-pairs signed-rank test. Between-group proportions will be compared by chi-square or Fisher exact test, while between-group comparisons for continuous variables will be done using either the unpaired 2-sided *t* test or the 2-sided Wilcoxon 2-sample test for nonnormal data. Correlations will be computed using Pearson or Spearman coefficients.

The primary analysis will be performed by comparing mean changes from T0 to T1 in the primary and secondary study outcomes. In particular, the MS-FIT group will be compared with the control group with analyses of covariance. The model includes change as the dependent variable, with the intervention group as the main effect and baseline and number of sessions as additional covariates. Finally, generalized estimating equation models will be performed to assess the persistence of the intervention effect; here the mean effect of the intervention at the time points T0, T1, and T2 on all outcomes, adjusted for the baseline value, will be evaluated between the 2 groups.

Differences in the outcome measures between subgroups defined by different polymorphisms will be analyzed using the analysis of variance or the Kruskal-Wallis test, as appropriate.

Statistical analysis will be performed using STATISTICA 7.1 software (StatSoft GmbH). Significance will be recognized for *P*<.05.

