### Intervention

All participants will be allowed to continue their leisure-time physical activities.

Participants in the MS-FIT group will receive the MS-FIT exergame [28]. They will be required to train at home with MS-FIT for 12 weeks by performing the exercises for a total of 30 minutes/day for at least 3 days/week.

While gaming, participants will choose their favorite and most useful exercises; the difficulty of the exercise will increase based on the user’s performance. In this way, the exercise selection and the reward structure will ensure the personalization of the intervention.

Before starting the intervention, each participant will be trained in the use of the tool by the study manager.

Participants in the control group will not receive MS-FIT; however, as a reward for their participation, we will offer them the MS-FIT intervention at the end of their study involvement.

All participants will be assessed at T0, T1, and T2.

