#### Other Measures

Adherence to the intervention will be provided by the number of sessions actually performed as automatically recorded by the MS-FIT tool and the number of dropouts.

Safety will be assessed by the number of potential issues (ie, number of falls). The severity of adverse events will be graded according to the Common Terminology Criteria for Adverse Events v 4.0 on a 5-point scale (grade 1, mild discomfort; grade 2, moderate discomfort; grade 3, severe inability; grade 4, life-threatening or disabling; grade 5, death) and reported in detail on the eCRF. A grade higher than grade 2 will be considered as a condition for dropout.

We will also collect information on the pharmacological treatments (specific and nonspecific for MS) followed by participants, comorbidities, and the type of PA practiced during participation in the study.

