## Discussion

### Summary

Cumulative data suggest that the Pilates method has proven beneficial in several neurological diseases and may be a PA tool for people with MS. A recent review [22] in MS showed that Pilates improves balance, gait, physical-functional conditions (muscle strength, core stability, aerobic capacity, and body composition), and cognitive functions; in contrast, fatigue, QoL, and psychological function did not show a clear improvement. Furthermore, high adherence (average adherence ≥80%) and few adverse effects were reported. For these reasons, future research is needed to develop clinical protocols that can maximize the therapeutic effects of Pilates for people with MS. In this context, novel devices and technologies for home-based interventions could provide solutions to overcome limitations due to urban barriers (eg, transportation), daily activities (eg, working time), and clinical conditions (eg, level of disability) and to ensure continuity of care. Therefore, practicing Pilates at home through eHealth tools could help people with MS to regularly engage in PA and to successfully maintain their physical, cognitive, and emotional status.

Here, we describe the RCT protocol designed to test the efficacy of a home-based PA intervention delivered through the MS-FIT exergame on balance and gait. In addition, we will also assess the effects on cognition, QoL, and well-being.

The present RCT protocol was designed taking into account previous studies in the MS scientific literature in terms of the number of weeks of intervention, weekly frequency, session duration, outcomes, setting, and control group [22]. Because only one study evaluated long-term monitoring after the intervention [58] and it is unclear whether the obtained results are maintained, as an additional element of novelty, we propose to schedule a follow-up assessment in order to define whether the effects of Pilates persist.

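### The primary ANCOVA adjusts the group effect for MS-FIT sessions, which controls cannot have, so it does not estimate the intention-to-treat effect and loses most of its power

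*Protocol article*

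**What the plan says.** The protocol article (Methods, Statistical Analysis) fixes the main comparison: "The primary analysis will be performed by comparing mean changes from T0 to T1 in the primary and secondary study outcomes". The groups are compared by analysis of covariance on change, "with the intervention group as the main effect and baseline and number of sessions as additional covariates". The same section states: "The study hypotheses will be tested using an intention-to-treat analysis", with all randomised patients included.

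Sessions are defined only under Other Measures, as part of adherence: "the number of sessions actually performed as automatically recorded by the MS-FIT tool". The Intervention section says: "Participants in the control group will not receive MS-FIT"; controls are offered it only once their involvement has ended. The MS-FIT arm is asked to "train at home with MS-FIT for 12 weeks by performing the exercises for a total of 30 minutes/day for at least 3 days/week".

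Nothing in the article confines the session term to a secondary, within-arm or dose-response analysis.

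**The concern.** The covariate is measured after randomisation and is a count of the treatment received. It varies only in the MS-FIT arm. Adjusting for it removes from the group term whatever part of the benefit rises with use, and leaves the model to estimate the effect of being assigned MS-FIT and never using it. The study aim is a different quantity: MS-FIT plus leisure-time activity against leisure-time activity alone, in everyone randomised.

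This model governs the Timed Up and Go (TUG) result and every secondary outcome. Followed as written, it could easily miss an effective intervention. Where adherence tracks prognosis, it could also show a group difference that the intervention did not cause.

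**Working it through.** **Inputs from the protocol article**
- TUG effect 1.8 s, SD 3.4 s, 80% power, two-sided 5%, 15% loss, 63 per arm (Sample Size).
- 1:1 allocation (Study Design).
- 108 T1 visits so far, about 54 per arm if balanced (Results).
- At least 3 days a week for 12 weeks, so 3 × 12 = 36 sessions or more (Intervention).

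**Assumptions.** The article gives neither the mean nor the SD of sessions. I take a mean of 36 (full prescription) or 29 (0.8 × 36, using the adherence of at least 80% that the Discussion reports for earlier Pilates studies), and vary the SD.

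**The plan's own figure.** n per arm = 2 × [3.4 × (1.96 + 0.84) / 1.8]² = 56.01, or 57. Dividing by 0.85 gives 66 unrounded-first, or 68 from 57, against the stated 63. With 63 × 0.85 = 53.55 completers per arm, power is 78.2%. This small shortfall does not affect the point below.

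**What the group coefficient means.** With sessions S = 0 in all controls, the slope b on S is identified only in the MS-FIT arm. Leaving baseline aside,

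group coefficient = (MS-FIT mean − b × mean S) − control mean.

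This is the MS-FIT line read off at S = 0. Centring S does not change it in this additive model.

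**Precision.** With m and s the mean and SD of S in the MS-FIT arm and n per arm,

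Var = σ² [1/n + 1/n + m²/(n s²)], so the variance ratio to the model without S is 1 + (m/s)²/2.

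Power for a 1.8 s effect that does not depend on sessions, at 53.55 per arm (78.2% without the covariate):

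| Mean S | SD S | Variance ratio | SE ratio | Power |
|---|---|---|---|---|
| 36 | 6 | 19.0 | 4.4 | 10% |
| 36 | 9 | 9.0 | 3.0 | 15% |
| 36 | 12 | 5.5 | 2.3 | 22% |
| 36 | 18 | 3.0 | 1.7 | 35% |
| 29 | 9 | 6.2 | 2.5 | 20% |
| 29 | 12 | 3.9 | 2.0 | 28% |
| 29 | 18 | 2.3 | 1.5 | 44% |
| 29 or 36 | equal to mean | 1.5 | 1.2 | 61% |

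Over SD 5 to 14, the SE ratio runs from √(1 + (36/5)²/2) = 5.2 to √(1 + (29/14)²/2) = 1.8, and power from about 8% to 34%. At mean 36 and SD 9, 80% power would need 56.01 × 9 = 504 per arm.

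**Dose-response** (simulation, 54 per arm, 2,000 runs per scenario; mean/SD pairs 36/6, 36/9, 29/9, 29/15)
- Benefit wholly proportional to sessions: mean group estimate about 0 s, rejection about 5%. Without the covariate the estimate is 1.8 s and power 75–77%.
- Half of the benefit proportional: estimate 0.9 to 1.0 s, power 7–14%.

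**Bias.** Suppose there is no true effect, but sessions correlate −0.3 with TUG change in the MS-FIT arm because adherent patients do better anyway. The coefficient is then biased by 0.3 × 3.4 × m/s:
- 36/9: 4.1 s (simulated 4.0)
- 29/9: 3.3 s (simulated 3.3)
- 29/15: 2.0 s (simulated 2.0)

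The bias is against MS-FIT. Two-sided rejection is 45–52% instead of 5%. Without the session term it stays at about 5%.

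**The case against.** Several points can be made for the plan.

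- *Zero in controls is inferred.* True: the article does not say how the count is coded for controls. The alternative is no better. If it is missing, a complete-case ANCOVA drops every control and no group effect can be estimated.
- *The size of the loss rests on assumed session counts.* True. A wide spread, for example with early leavers in the intention-to-treat set, softens it: 44% at mean 29 and SD 18, 61% in the extreme case of SD equal to the mean. With all 63 per arm, power without the covariate is 84%, and those two cases become 50% and 68%. Power still falls in every scenario tried.
- *The group term goes to zero only under strict proportionality.* True: with half the benefit proportional, about half the effect remains. It is still not the randomised effect.
- *Other analyses omit sessions.* The section also lists unpaired two-group tests, and a generalised estimating equation model adjusted only for baseline. But the two-group tests are listed generically and the latter model is assigned to persistence of effect. Neither replaces the ANCOVA as the stated primary comparison, although both would give estimates free of this defect.

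These points limit how precisely the damage can be stated. None of them supports keeping the term in the primary model.

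**Conclusion.** The concern holds. As written, the primary model estimates the effect of MS-FIT at zero sessions, or nothing at all if controls are coded missing, and this contradicts the intention-to-treat principle in the same section. That conclusion does not depend on any assumed figure.

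The size does. With session means of 29 to 36, SDs of 5 to 14 and about 54 per arm, power drops from about 78% to 8–34% if the effect is unrelated to use, and to about 5% if it is proportional to use. If adherence is related to prognosis, the coefficient is also confounded: at an assumed correlation of −0.3, by 2 to 4 s, which is larger than the 1.8 s effect the trial was sized on. This should be corrected before the analysis is run.

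**What to change.** Delete the number of sessions from the between-group models for the primary and secondary outcomes. The primary model becomes T0 to T1 change (or the T1 value) on group and baseline value, in the intention-to-treat set.

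If dose-response is of interest, describe it separately and label it exploratory. Two options are a regression on sessions within the MS-FIT arm only, read as an association, or a complier-average causal effect with randomisation as the instrument. The choice between them is open; removing the covariate from the primary comparison is not.

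The text change is about one sentence and needs no new data. Under Ethical Considerations it needs the agreement of all investigators, signature at each site, ethics committee submission and a registry update. The Results section already reports 108 T1 and 103 T2 visits and expects publication in early 2025, so the change should be dated and documented before the group comparison is made. If the comparison has already been run, report the change openly as a deviation and show the results of both models.

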## Methods

### Study Design

We are conducting a multicenter 2-arm, superiority randomized controlled trial (RCT) with 3 assessment points (baseline, T0; postintervention at 12 weeks, T1; and follow-up at 6 weeks, T2). Participants will be allocated to the intervention (MS-FIT) or control group in a 1:1 ratio by simple randomization.

Participants in the MS-FIT group will have access to the MS-FIT exergame for at-home self-administration [28] (Multimedia Appendix 1) in addition to their leisure-time physical activities. Participants in the control group will have the possibility to perform only their leisure-time physical activities. Exercise will not be allowed and rehabilitation treatments, except for speech therapy, sphincter rehabilitation, and psychological support, must be suspended. The study design is illustrated in Figure 1.

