### Sample Size

The sample size was calculated by referring to the TUG change after a Pilates intervention found by Kalron et al [30] in a group of people with MS. The authors found no difference between the group receiving the Pilates intervention and the control group receiving an intervention of physical therapy. The Pilates group improved the TUG performance by about 1.8 seconds, which is clinically relevant for people with MS. Considering a variability of about 3.4 seconds, a power of 80%, a significance level (2-sided) of 5%, and a potential loss of 15% of patients at follow-up, the estimation of the necessary sample size consists of approximately 63 participants for the experimental group (a total of 126).

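### The GEE for persistence lists T0 as an effect time point and as the covariate and names no T2 contrast; run as one pooled group effect, it would not answer whether the effect lasts

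*Protocol article*

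**What the plan says.** The Study Design section sets three visits: "baseline, T0; postintervention at 12 weeks, T1; and follow-up at 6 weeks, T2". The Statistical Analysis section makes the primary analysis an analysis of covariance of the change from T0 to T1. As the last step it states that "generalized estimating equation models will be performed to assess the persistence of the intervention effect", and it describes the quantity to be compared between the groups as "the mean effect of the intervention at the time points T0, T1, and T2 on all outcomes, adjusted for the baseline value". It names neither a group-by-time term nor a comparison at T2.

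The Summary in the Discussion says what the follow-up visit is for: "we propose to schedule a follow-up assessment in order to define whether the effects of Pilates persist". It presents this as a further new feature of the trial. The GEE is the only analysis that the article assigns to that question.

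**The concern.** Persistence is a question about T2: is there still a difference between the groups six weeks after training has ended? The sentence describes a mean effect over a list of visits that includes T0, which precedes treatment, and T1, which is the end of treatment. Taken as one pooled group effect, this raises two distinct problems.

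- **T0.** Under randomization the expected group difference at T0 is zero. Counting that visit in the mean pulls the estimate towards zero.
- **T1 with T2.** A mean over these two visits cannot tell an effect that lasts from one that is present at the end of training and then gone. A significant result could come from T1 alone.

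At stake is the trial's statement about durability, for every outcome, because the sentence applies the GEE to all of them. The size of a lasting effect could be understated, and persistence could be declared where none exists.

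**Working it through.** The plan gives no figure for the GEE, so there is nothing of its own to reproduce. The inputs come from its Sample Size and Results sections.

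**Inputs from the document**
- Effect: 1.8 s ("The Pilates group improved the TUG performance by about 1.8 seconds").
- SD 3.4 s and two-sided 5% level. The text does not say whether 3.4 s is the SD of the raw score or of the change.
- Patients: "approximately 63 participants for the experimental group (a total of 126"), with "a potential loss of 15% of patients at follow-up". This leaves 63 × 0.85 = 53.55 per arm. The Results section reports 108 T1 visits, or 54 per arm. I use n = 54.

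**Assumptions not in the document:** equal within-patient correlation ρ of 0.5 to 0.8 between visits, equal SD at each visit, complete data, robust standard errors.

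**Step 1. Expected pooled estimate (effects at T0, T1, T2)**
- Effect fully kept: (0 + 1.8 + 1.8)/3 = 1.2 s, two thirds of the truth.
- Effect at T1 only: (0 + 1.8 + 0)/3 = 0.6 s.
- Half kept at T2: (0 + 1.8 + 0.9)/3 = 0.9 s.

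These values need no correlation or SD.

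**Step 2. What the T0 row does to the test**

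A patient's mean over three visits is (1/3) × T0 + (2/3) × mean(T1, T2). After adjustment for T0 with one slope, the first term contributes nothing to the group coefficient. The pooled estimate is therefore 2/3 of the T1/T2 estimate, and its standard error is also 2/3, so the test statistic does not change. Simulation agrees: rejection rates were identical with and without the T0 row. T0 distorts the size, not the P value.

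**Step 3. How often an effect at T1 only is significant**

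With T0 dropped, the pooled T1/T2 effect is (1.8 + 0)/2 = 0.9 s. The residual variance of mean(T1, T2) given T0 is σ²[(1+ρ)/2 − ρ²]. The SE is √(2 × residual variance/54), and the rejection rate is about Φ(0.9/SE − 1.96). If 3.4 s is the SD of change, σ² = 11.56/[2(1−ρ)]; if it is the raw SD, σ² = 11.56.

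| 3.4 s read as | ρ | σ² | Residual variance | SE | 0.9/SE | P<.05 |
|---|---|---|---|---|---|---|
| either (they coincide) | 0.5 | 11.56 | 5.78 | 0.463 | 1.95 | 49% |
| change SD | 0.7 | 19.27 | 6.94 | 0.507 | 1.78 | 43% |
| change SD | 0.8 | 28.90 | 7.51 | 0.528 | 1.71 | 40% |
| raw SD | 0.7 | 11.56 | 4.16 | 0.393 | 2.29 | 63% |
| raw SD | 0.8 | 11.56 | 3.01 | 0.334 | 2.70 | 77% |

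Simulated GEEs (2000 trials per setting, independence and exchangeable working correlation) gave 40 to 66% over the first four rows. A separate simulation with raw SD 3.4 s and ρ from 0.5 to 0.8 gave 51 to 79%. Together the range is roughly 40 to 80%.

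**Step 4. The same data with a T2 contrast** (T1 and T2 as outcomes, T0 as covariate, group-by-time)
- Nothing left at T2: estimate about 0, significant in about 5 to 7% of simulated trials (nominal 5%).
- Fully kept: estimate about 1.8 s, power 83 to 97% over the first four rows. For example, with change SD and ρ = 0.8, SE = √(2 × 28.9 × 0.36/54) = 0.621 and Φ(1.8/0.621 − 1.96) = 83%.
- Half kept: estimate about 0.9 s, significant in 31 to 51%, against 73 to 93% for the pooled effect.

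**The case against.** The strongest reply is that the sentence need not mean one pooled number. A GEE models population means, and a mean effect at several listed visits can be read as a separate group difference at each. The stated purpose, persistence, fits that reading better. The T2 difference would then be unbiased with near-nominal error, and the averaging problem would fall away; only a redundant T0 row would remain. A condensed article may also leave model terms to a fuller document. This stands in part: a reader might infer that the plan definitely averages over the visits and that its test is therefore wrong, and the text does not establish that. But the sentence does more than omit detail. It puts T0 among the effect time points, uses the singular for the effect, and points to no comparison at T2.

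Three further inferences also go too far.
- That the T0 difference is zero by construction. With one baseline slope shared across visits, the adjusted difference at T0 itself is (1 − slope) times the chance baseline imbalance, which is zero only in expectation.
- That T0 among the outcomes is the source of false persistence. Step 2 shows it leaves the test alone, so deleting T0 without separating T1 from T2 would cure nothing there. T0 as an outcome is not a fault in itself either; the double use is.
- That the trial's main result is at risk. The GEE is secondary, and the stated aim is efficacy on Timed Up and Go, analysed from T0 to T1.

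**Conclusion.** The point holds as a badly specified secondary analysis. The text lists T0 both as an effect time point and as the covariate, and it does not tie persistence to T2. On the plain reading, a single pooled effect, a fully kept 1.8 s would be reported as about 1.2 s. An effect wholly gone by T2 would give about 0.6 s and reach P<.05 in roughly 40 to 80% of trials, where a T2 contrast would do so in about 5 to 7%.

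The 1.2 s and 0.6 s follow from the plan's own 1.8 s by simple averaging. The percentages rest on the assumed correlation of 0.5 to 0.8, on the unstated meaning of the 3.4 s, on 54 per arm and on complete data. On the visit-by-visit reading the false-persistence problem does not arise, and what is needed is clarification. The primary T0 to T1 analysis is not affected by this point on either reading.

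**What to change.** Reword the GEE sentence so that it admits one reading:

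- Outcomes at T1 and T2, with T0 as covariate only. Alternatively, keep T0 as an outcome in a model with a common T0 mean for both groups and no baseline covariate.
- Terms for group, time and group-by-time.
- Persistence defined as the adjusted between-group difference at T2, with its 95% CI.
- The change in effect from T1 to T2 reported beside it, and no effect averaged over T0.

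Both parts are needed: removing T0 corrects the size of the estimate, and separating T1 from T2 corrects the test. The cost is wording and model code. No new data or visits are required, and the article still places the analysis in the future.

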Recently, MS-FIT (HELAGLOBE Società a Relazioni Limitate), a Kinect-based playable exergame implementing Pilates exercises, has been developed by an Italian network of experts in the field of MS rehabilitation for future use in research and clinics [28]. It has been customized for people with MS, allows tailoring the intervention in order to potentiate the effects of an ongoing program, and has been conceived to be developed for asynchronous telerehabilitation purposes.

The aim of this study, promoted by the Italian Multiple Sclerosis Foundation, is to test in people with MS the efficacy on the mobility domain measured with the Timed Up and Go (TUG) test of a self-managed home intervention delivered through MS-FIT in addition to leisure-time physical activities, in comparison with leisure-time physical activities alone. Measures of balance, gait, upper limb functioning, PA, cognition, quality of life (QoL), well-being, acceptability, satisfaction with use, and adherence to the intervention will also be considered. In addition, a blood sample will be collected to investigate if genetic polymorphisms that are considered potential regulators of neural plasticity could influence the response to the proposed intervention [29].

Based on previous findings [30], we expect that the intervention, in addition to leisure-time physical activities, will be associated with a primary outcome of mobility (TUG) compared with leisure-time physical activities alone that are expected to worsen due to disease progression. Similar changes between groups are expected in secondary outcomes; furthermore, based on our previous findings [28], we expect high acceptability, satisfaction-to-use, and adherence to the MS-FIT intervention.

If results are positive, MS-FIT could be proposed in combination with rehabilitation to potentiate the effect of the rehabilitation intervention and ensure continuity of care for people with MS.

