#### Blood Sample

If the participant consents, a peripheral blood sample will be collected at T0 in vacutainer tubes containing ethylenediaminetetraacetic acid. According to previous studies [29], participants will be divided into subgroups with respect to polymorphism. All blood samples will be genotyped for a total of 55 genetic polymorphisms of 23 potential regulators, such as Homer1, AKT1, RAPTOR, D2R, GAPD, CHAT, p53, BRCA2, LIG4, XRCC5, CYP3A4, NBS1, MDM2, CNR1, ATTn, CNR2, GRIN1, GRIN2B, TRPV1, FAAH, COMPT, and BDNF.

For example, CNR1 region containing AAT repetitions will be amplified by polymerase chain reaction from genomic DNA; sequencing products will be purified using a rapid, high-performance dye-terminator removal kit and will be subjected to electrophoresis; AAT repetitions will be counted on the resulting electropherograms (short AAT: homozygous or heterozygous for an allele with ≤11 repeats of AAT triplets; long AAT: homozygous for an allele with ≥12 repeats of AAT triplets). For the TRPV1 and FAAH, the iPLEX Gold technology and MassARRAY high-throughput DNA analysis will be performed.

The blood sample will be collected early in the morning after awakening (8:00 AM). To synchronize the sample with lifestyle variables, participants were requested to avoid excessive physical activity in the last 3 days before blood sampling, to sleep for 7-8 hours the night before the study, to avoid starvation, and to have a normal breakfast in the morning [29]. The samples will be analyzed in the center of DC.

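### The planned genotype comparison has no group-by-genotype term, so it does not answer the stated question of whether polymorphisms influence response to MS-FIT (minor, ancillary aim)

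*Protocol article*

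**What the plan says.** - **Aim (Introduction).** Blood is collected to investigate if "genetic polymorphisms that are considered potential regulators of neural plasticity could influence the response to the proposed intervention".
- **Grouping (Blood Sample).** The text states that "participants will be divided into subgroups with respect to polymorphism". The split is by genotype and arm is not mentioned. The worked example for CNR1 forms two groups, short and long AAT.
- **Number (Blood Sample).** "All blood samples will be genotyped for a total of 55 genetic polymorphisms of 23 potential regulators". Sampling depends on the participant's consent.
- **Test (Statistical Analysis).** "Differences in the outcome measures between subgroups defined by different polymorphisms will be analyzed using the analysis of variance", with the Kruskal-Wallis test named as the alternative.
- **Threshold (Statistical Analysis).** One closing line covers the whole section: "Significance will be recognized for *P*<.05".

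The ANCOVA in the same section contains group, baseline and number of sessions. The generalized estimating equation models compare the two groups over time. Neither is described as containing a genotype term.

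**The concern.** Whether genotype influences response to MS-FIT means whether the MS-FIT-minus-control difference varies with genotype. The quantity of interest is therefore a difference of differences. The named test looks at a different quantity, the difference in outcome between genotype groups.

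At stake is how the genetic results can be interpreted. A polymorphism linked to TUG change in both arms would look the same as one that marks responders. A polymorphism whose association runs in opposite directions in the two arms could go unseen. The randomised control group is what allows these cases to be told apart, and the described test assigns it no role. The number of polymorphisms and the single unadjusted threshold add a second, smaller problem.

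**Working it through.** **Inputs from the article.** 55 polymorphisms of 23 regulators; threshold 0.05; 126 randomised 1:1; 108 with a T1 visit so far (Results); planning effect 1.8 s and SD 3.4 s (Sample Size). The number genotyped is not given and may be below 108, because sampling is optional.

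**Assumed.** Carrier share (0.4 or 0.5, with a range down to 0.1), size of the genotype effect, two genotype groups.

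**The plan's own figure.** The article gives no sample size or power for the genotype analysis. The nearest figure is 63 per arm for TUG. Its inputs give 2 x (3.4 x (1.960 + 0.842) / 1.8)^2 = 56.0 per arm, so 57 after rounding up. Dividing the unrounded 56.0 by 0.85 gives 65.9, close to but not exactly 63. Nothing below depends on that gap.

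**1. Prognostic-only genotype.** Let the genotype shift the outcome by d SD in both arms, with no modification. The pooled two-group comparison has signal d x sqrt(N p (1-p)). With N = 108 and p = 0.4 this is d x sqrt(25.92) = 5.09 d.

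| d (SD) | Signal | Pooled ANOVA significant, simulated | Interaction test |
|---|---|---|---|
| 0.1 | 0.51 | 8% | about 5% |
| 0.2 | 1.02 | 18% | about 5% |
| 0.3 | 1.53 | 33% | about 5% |
| 0.4 | 2.04 | 51% | about 5% |
| 0.6 | 3.05 | 84% | about 5% |

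The simulation used 4,000 runs per row. On the article's SD, 0.6 SD is 0.6 x 3.4 = 2.04 s, more than the whole 1.8 s planning effect, so the last row is an extreme. At 0.6 SD, Kruskal-Wallis gives 81%, and ANOVA within the MS-FIT arm alone gives 55%. Restricting to one arm therefore does not cure the problem.

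**2. Prognosis and modification look alike.** Take a 1.8 s shift in both arms. Then take a 3.6 s shift in the MS-FIT arm only, with none in controls. With equal arms, the pooled genotype difference is (1.8 + 1.8)/2 = 1.8 s in the first case and (0 + 3.6)/2 = 1.8 s in the second. The pooled comparison estimates the same difference in both.

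**3. A modifier can be missed.** Let the genotype difference be +1.8 s under MS-FIT and -1.8 s under control, so that treatment effects differ by 3.6 s and the average genotype effect is zero (N = 108, p = 0.5). Pooled ANOVA is significant in 4% of runs and the interaction test in 76%. This case was built so that the two arms cancel. A modifier that acts only in the MS-FIT arm would still show in the pooled test, but could not be identified as one (step 2).

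**4. Multiplicity, if all 55 are tested on one outcome and none has an effect.**
- Expected false positives: 55 x 0.05 = 2.75, whatever the correlation.
- Chance of at least one: 1 - 0.95^55 = 94% if independent; 1 - 0.95^23 = 69% with 23 effective tests; 1 - 0.95^10 = 40% with 10.

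**5. Power of the interaction test.** SE = SD x sqrt(2/(n p) + 2/(n(1-p))), with n per arm. With n = 63 and p = 0.5, SE = 3.4 x sqrt(4/31.5) = 1.21 s. The SE of the arm effect is 3.4 x sqrt(2/63) = 0.61 s.
- For a 1.8 s difference in treatment effect, 1.8/1.21 = 1.49. Power is Phi(1.49 - 1.96) = 32% at 0.05 and about 3% at 0.05/55 = 0.00091.
- For carrier shares from 50% down to 10%, power at 0.05 falls from 32% to 14% with N = 126, and from 28% to 13% with N = 108.

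**The case against.** The genetic work is ancillary. It is introduced as an addition, rests on optional consent, and is not listed among the primary or secondary outcomes. An analysis plan that is not shown may hold the detail. Analysis of variance need not be one-way, and a factorial version could carry an interaction. These points stand as far as importance goes. They do not remove the mismatch: the article names the test itself, the alternative it names (Kruskal-Wallis) has no interaction term, and no model in the section combines arm and genotype.

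Some stronger readings are tempting, but the article does not support them.
- **That 55 unadjusted tests will be run on every outcome, making false positives almost certain.** The article says 55 will be genotyped, not that all will be tested or on which outcomes. The threshold is a general closing line, and a multiplicity rule for an ancillary analysis may sit in an unseen plan. Even for 55 tests, the 94% needs independence, which is doubtful when they fall in 23 regulators.
- **That the control arm will be left out.** The article does not say which arms enter the comparison.
- **That prognostic markers will be reported as responder markers.** No reporting rule is stated. The article only leaves the two indistinguishable.
- **That an interaction test would rescue the aim.** It asks the right question, but with little power at this sample size.

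**Conclusion.** The point holds, as a minor one. The test written in Statistical Analysis does not address the aim written in the Introduction, whether it is run on both arms pooled or on the MS-FIT arm alone. This follows from the text and needs no numerical assumption.

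The size of the problem does rest on assumptions. A prognostic-only genotype passes the pooled test about 8% of the time at 0.1 SD and about 84% at 0.6 SD. Neither the effect sizes nor the carrier share comes from the article, and 108 is an upper guess at the number genotyped among those with T1 data so far. The multiplicity figures (2.75 expected; 40% to 94% for at least one) apply only if all 55 polymorphisms are tested on a single outcome and none has an effect. Neither the primary TUG comparison nor the trial's main conclusion is touched.

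**What to change.** For each polymorphism tested, model T0-T1 TUG change on group, genotype, group x genotype and baseline TUG, and take the interaction as the test of the aim. State the genotype coding and the list of polymorphisms before the genotype data are analysed. Control the false discovery rate across the polymorphisms tested. Report the treatment effect by genotype and the interaction with confidence intervals. Label the whole analysis exploratory. If other outcomes are examined, give estimates and intervals only.

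**Cost.** Wording in the analysis plan, with no new samples or visits: the control group is already randomised, and the article genotypes all blood samples collected. There will be fewer nominally significant genotype findings. The plan should also say openly that power is low: about 32% at 0.05 for a 1.8 s difference in treatment effect (N = 126, 50% carriers assumed), about 3% at 0.05/55, and less with fewer genotyped participants or rarer variants. A null result would therefore not show that genotype is irrelevant.
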